### Sample size calculation

2.3

The target sample size for this PRCT was rooted on a previous research (17). The required sample size was determined by calculating the minimum number of participants needed to detect a clinically meaningful difference between the intervention and control groups, specifically for the primary outcome measure, using a superiority design. The effect size (Cohen’s d) was estimated at 0.5, representing a moderate difference we aimed to detect. Assuming an alpha level (*α*) of 0.05 (two-sided) and a statistical power (1 − *β*) of 80% (0.80), the required number of participants per group (n) was calculated using the formula for comparing two independent means: *n* = 2 × *δ*2(Zα/2 + Zβ)2 × *σ*2, where Zα/2 and Zβ are the standardized normal deviates corresponding to the significance level and power, σ is the estimated standard deviation, and δ is the minimum clinically important difference. We estimated the standard deviation (σ) to be 10 points and set the minimum detectable difference (δ) to be 5 points on the primary outcome scale. Accounting for an anticipated 15% attrition rate, the total required sample size was adjusted from N_calculated_ to N_final_ to ensure adequate power at the study’s conclusion, resulting in a target enrollment of 74 participants (37 per group). Target sample sizes are listed in Table 2. This trial is powered for a superiority outcome, but a secondary, exploratory non-inferiority (NI) analysis is planned to assess the comparative effectiveness or safety of the intervention if the superiority hypothesis is not met. This approach is clinically relevant for pragmatic trials, evaluating whether the intervention is “not worse” than the control within a predefined NI margin (*Δ*). However, the sample size of 74, calculated for superiority, is likely insufficient for a definitive NI trial, as NI analyses typically require larger samples to ensure the confidence interval of the treatment difference lies within Δ. To address this, the manuscript will clarify that the NI analysis is exploratory and hypothesis-generating, underpowered for this endpoint, and will report the NI margin and two-sided 95% confidence interval for the primary outcome difference.

**Table 2 tab2:** Target sample size of the study.

Category	Control group	Intervention group	Total participants
Efficacy evaluable cases	33	33	66
Total sample size (incl. 10% dropout)	37	37	74

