### Outcome measures

2.6

This study used a comprehensive set of outcome measures to evaluate the effectiveness and safety of the interventions. All patient-reported outcomes were assessed at specific visits throughout the study.

(1) NRS scores for pain intensity (low back and radicular pain).

At weeks −1 (baseline), 0, 3, 5, 7, 12, 19, and 26, participants will assess their low back pain and radiating leg pain over the past week using an 11-point Numeric Rating Scale (NRS), ranging from 0 (no pain) to 10 (worst pain imaginable), selecting the number that best reflects their current discomfort level.

(2) Oswestry disability index.

At weeks 0, 3, 5, 7, 12, 19, and 26 visits, participants will complete the ODI (19) questionnaire by providing answers to each question.

(3) VAS score for pain intensity (low back and radicular pain)

At weeks 0, 7, 12, 19, and 26, participants will use a 100 mm Pain Visual Analog Scale (VAS) (20) to quantify their LBP experienced over the past week. Participants will indicate their current pain level by marking a point on a 100 mm Visual Analog Scale (VAS), ranging from “no pain” to “worst pain imaginable”.

(4) Roland-Morris disability questionnaire (RMDQ)

At weeks 0, 7, 12, 19, and 26, the participants will complete the Roland-Morris Disability Questionnaire (RMDQ) (21) by answering each question.

(5) EuroQol-5 dimension-5 level (EQ-5D-5L)

At Weeks 0, 3, 7, 12, 19, and 26, the participants will complete the EQ-5D-5L (22) questionnaire by responding to each question.

(6) Health-related quality of life instrument with eight items (HINT-8)

At weeks 0, 3, 7, 12, 19, and 26, participants will complete the HINT-8 questionnaire (23). Participants will assess their health status over the past week by selecting one of four response levels for each question, ranging from 1 (e.g., “not at all” for climbing stairs or “not at all depressed” for depression) to 4 (e.g., “unable to climb” or “always depressed”).

(7) Global perceived effect (GPE)

At weeks 3, 7, 12, 19, and 26, participants completed the Global Perceived Effect (GPE) questionnaire (24) by providing answers to each question.

(8) Patient health questionnaire-15 (PHQ-15)

At weeks 0, 7, 12, 19, and 26, participants will complete the Korean version of the Patient Health Questionnaire-15 (PHQ-15). This tool, a 15-item condensed version (25) developed by Kroenke et al. from Spitzer et al.’s PHQ (26), assesses general health status and subjective somatic symptoms.

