#### Analysis of efficacy endpoints

2.7.2

1) Primary efficacy endpoint

Changes in Numeric Rating Scale (NRS) for radiating pain and Oswestry Disability Index (ODI) from baseline to week 7 will be analyzed using a Linear Mixed Model, with group as a fixed factor and relevant baseline covariates. Missing data will be handled via Mixed Model for Repeated Measures (MMRM), with sensitivity analyses using ANCOVA on datasets imputed by multiple imputations (MI) and Last Observation Carried Forward (LOCF).

2) Secondary efficacy endpoints

Changes in NRS for low back pain, 100 mm Pain Visual Analog Scale (VAS), Roland-Morris Disability Questionnaire (RMDQ), EuroQol 5-Dimension 5-Level (EQ-5D-5L), Health Information National Trends Survey (HINT-8), Global Perceived Effect (GPE), Patient Health Questionnaire-15 (PHQ-15), economic measures, and Kidney Yin Deficiency Pattern Identification Questionnaire (DSKI) scores will be analyzed using a Linear Mixed Model with baseline covariates. Missing data will be managed via MMRM, with ANCOVA sensitivity analyses using MI and LOCF. Non-inferiority testing, with margins of −1.75 (NRS) and −10 (ODI), will be conducted if superiority is not achieved, considering herbal medicine non-inferior if the 95% confidence interval lower bound does not exceed these margins.

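### The non-inferiority rule in section 2.7.2 is worded in reverse and contradicts section 2.3; only one of its four readings, probably the intended one, is valid

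*Protocol article*

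**What the plan says.** Section 2.7.2 of the protocol article, under the secondary efficacy endpoints, gives the margins and the trigger: "Non-inferiority testing, with margins of −1.75 (NRS) and −10 (ODI), will be conducted if superiority is not achieved". The decision rule follows in the same sentence: "considering herbal medicine non-inferior if the 95% confidence interval lower bound does not exceed these margins".

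The variables concerned are defined just above as "Changes in Numeric Rating Scale (NRS) for radiating pain and Oswestry Disability Index (ODI) from baseline to week 7". Section 2.6 describes the NRS as running from no pain at 0 to the worst pain at 10, so a higher score is worse. ODI is a disability index and is taken here in the same direction. The article does not say whether the group difference is herbal minus control or the reverse, nor whether improvement is scored as positive.

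Section 2.3 describes the same analysis in other terms. Its purpose is "evaluating whether the intervention is “not worse” than the control within a predefined NI margin", and the aim is "to ensure the confidence interval of the treatment difference lies within Δ". It also fixes the status: "a secondary, exploratory non-inferiority (NI) analysis is planned".

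**The concern.** Two things are unsettled in the sentence that states the rule.

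- **The verb.** In ordinary numerical language, a bound that does not exceed −10 is a bound of −10 or lower. When positive favours herbal medicine, which is the convention that fits a negative margin and a lower bound, that is the result in which non-inferiority fails. It is also the opposite of section 2.3, where the interval has to stay inside the margin.
- **The sign.** Taking the verb to mean extending beyond the margin repairs the rule only if positive favours herbal medicine. The endpoint is change on scales where higher is worse. If the difference is taken as herbal minus control on those change scores, harm lies on the upper side. A lower bound above −10 then shows only that herbal medicine is not better by more than 10 points.

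At stake is whether a result that is clearly worse than the margin could be reported as non-inferior. The trigger does not exclude this: superiority is also not achieved when herbal medicine is significantly worse, so the rule would be applied there too. If the direction is settled only after the results are known, the verdict can depend on that choice.

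**Working it through.** The article attaches no error rate or power to the non-inferiority rule, so there is no stated figure to reproduce for it. The check works out how often each reading would declare non-inferiority.

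**Inputs**
- Evaluable participants: 33 per arm (Table 2). The step to enrolment agrees with the table: 33/0.90 = 36.7, rounded up to 37.
- SD 10 points (section 2.3). The scale is not named there; it is assumed here to be ODI.
- Margins: 10 for ODI and 1.75 for NRS (section 2.7.2, absolute values).
- Two-sided 95% CI (section 2.7), multiplier 1.96.
- SD of NRS change: not given. Assumed 2, with a range of 1.5 to 2.5.

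**Precision**
- SE = SD × √(2/33). For ODI this is 10 × 0.2462 = 2.462, and the CI half-width is 1.96 × 2.462 = 4.83.
- For NRS with SD 1.5, 2 and 2.5, the SE is 0.369, 0.492 and 0.615, and the half-width is 0.72, 0.97 and 1.21.

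**Formulas (normal approximation)**

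Let μ be the true difference on the scale in use, and m the margin without its sign.
- Literal reading, lower bound ≤ −m: P = Φ((−m + 1.96·SE − μ)/SE).
- Loose reading, lower bound > −m: one minus that.

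**ODI, m = 10**
- Literal, positive = herbal better, herbal 10 points worse (μ = −10): Φ((−10 + 4.83 + 10)/2.462) = Φ(1.96) = 97.5%.
- Literal, arms equal (μ = 0): Φ((−10 + 4.83)/2.462) = Φ(−2.10) = 1.8%.
- Literal, herbal minus control change, herbal 10 points worse (μ = +10): Φ((−10 + 4.83 − 10)/2.462) = Φ(−6.16), about 0%.

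| Reading of the rule | Sign of the difference | Declared, herbal 10 points worse | Declared, arms equal |
|---|---|---|---|
| Literal (≤ −10) | positive = herbal better | 97.5% | 1.8% |
| Literal (≤ −10) | herbal minus control change | about 0% | 1.8% |
| Loose (> −10) | positive = herbal better | 2.5% (valid rule) | 98.2% |
| Loose (> −10) | herbal minus control change | over 99.9% | 98.2% |

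**Example.** Herbal medicine is observed 15 ODI points worse.
- With positive meaning better, the CI is −15 ± 4.83, or −19.8 to −10.2. It lies wholly beyond the margin, yet the literal rule passes it. The equal-arms interval, −4.8 to +4.8, fails the literal rule.
- On herbal minus control change scores the CI is +10.2 to +19.8. The loose rule passes it, because it inspects the wrong end.

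**NRS, m = 1.75**
- At a true deficit of 1.75, the three readings that differ there give the same picture for every SD from 1.5 to 2.5: 97.5% (literal, positive = better), 2.5% (valid reading) and over 99.9% (loose, herbal minus control change).
- With equal arms, the literal rule declares non-inferiority in 0.3%, 5.5% and 19% of trials for SD 1.5, 2 and 2.5. The valid rule does so in 99.7%, 94% and 81%.

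**Dependence on the SD.** The 97.5% and 2.5% at the margin follow from the 1.96 multiplier alone and hold for any SD. Only the equal-arms figures move much: with an ODI SD of 15, the literal rule gives 22.7% in place of 1.8%.

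**The case against.** The strongest answer is that the intent can be recovered. A negative margin paired with a lower bound is coherent only if positive favours herbal medicine. Section 2.3 speaks of not being worse within the margin and of an interval inside it. Read together, the two sections suggest that the bound must not go beyond the margin, and that is the correct rule. This stands. A reader might infer that the rule gives a wrong verdict however it is read, but the documents do not support that, because one coherent reading controls the error at 2.5%.

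It is also fair that the direction of subtraction is often left to a full protocol or analysis plan, neither of which is shown. The missing sign alone would be weak ground. But the article does state a decision rule, the rule is reversed as worded, and the sign is what decides whether the charitable reading of the verb rescues it.

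The last objection concerns weight. A reader might infer that this rule will decide the trial's main conclusion. Section 2.3 says otherwise: it calls the analysis exploratory, hypothesis-generating and underpowered, and commits to reporting the margin and the two-sided 95% CI. A reader of the report could therefore see a mislabelled result. That lowers the severity. It does not make a reversed criterion acceptable, and the abstract and section 2.7.2 announce the test without the exploratory label.

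Finally, the high percentages describe what each reading would do if applied. They are not the probability that an analyst would apply it.

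**Conclusion.** The point holds as a defect of wording with a real consequence. The rule in section 2.7.2 is reversed when read literally and contradicts section 2.3. It becomes valid only under two conditions that the article does not state: that exceeding means extending beyond, and that positive differences favour herbal medicine. That reading is probably what was meant.

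Of the four readings, one is correct, two would usually declare non-inferiority when herbal medicine is worse by the full margin, and one is not falsely favourable but almost never declares non-inferiority even when the arms are equal.

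The sizes rest on 33 evaluable per arm, a normal approximation, the stated SD of 10 applied to ODI, and an assumed NRS SD of 1.5 to 2.5. The direction of the error depends on none of the SDs. Because the analysis is exploratory and follows only if superiority is not achieved, severity is moderate.

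**What to change.** Replace the rule in section 2.7.2 with one that fixes both the sign and the bound, for example:

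*Difference = herbal minus control in week-7 change (positive = herbal worse). Herbal medicine is non-inferior if the upper limit of the two-sided 95% CI is below +1.75 (NRS) or +10 (ODI).*

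The mirror image is equivalent: *control minus herbal; lower limit above −1.75 (NRS) or −10 (ODI).*

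Use the same direction in section 2.3, the analysis plan and the report, and settle it before any comparative results are seen. The cost is one sentence in section 2.7.2 with matching text elsewhere. Recruitment, data collection and sample size are unaffected.

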#### Analysis of safety endpoints

2.7.3

Adverse events (AEs), including those leading to withdrawal and serious AEs, will be summarized by treatment group and compared using chi-squared or Fisher’s exact test. Incidence rates of all AEs and herbal medicine-specific AEs will be reported.

#### Cost-effectiveness analysis

2.7.4

Economic evaluation will adopt a societal perspective, using a micro-costing approach to compare intervention and control groups over the follow-up period. The Incremental Cost-Effectiveness Ratio (ICER) will be calculated as the cost difference (ΔC) divided by the Quality-Adjusted Life Years (ΔE) difference from EQ-5D-5L scores. Costs include direct medical (e.g., procedures, hospitalization), direct non-medical (e.g., transportation), and indirect costs (e.g., productivity loss). Non-parametric bootstrapping (1,000 replications) will estimate ICER confidence intervals, presented on a Cost-Effectiveness Plane, with a Cost-Effectiveness Acceptability Curve illustrating cost-effectiveness probabilities across willingness-to-pay thresholds.

#### Missing value management

2.7.5

Missing data for primary and secondary outcomes will be managed using LOCF imputation, selected for its conservative approach in estimating treatment effects post-dropout, assuming stable participant conditions after the last observation, ensuring robust and interpretable efficacy results.

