### Statistical analysis

2.7

Data will be analyzed using intention-to-treat (ITT) and per-protocol (PP) sets. The ITT population includes all randomized participants receiving at least one dose of herbal medicine or one traditional Korean medicine (TKM) session. The PP population comprises ITT participants with ≥70% herbal medicine compliance or ≥7 TKM sessions. Efficacy outcomes will be assessed in both ITT and PP populations, with ITT as the primary analysis and PP as supportive. Demographic and safety evaluations will use the ITT population, with safety analyses based on raw data without imputation. Statistical analyses will be conducted using SAS version 9.4 (SAS Institute, Cary, NC, United States) with a two-sided significance level of 0.05 and 95% confidence intervals.

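### Sections 2.7.2 and 2.7.5 name different main missing-data methods (MMRM and LOCF) for the same outcomes, and the reason given for LOCF does not hold in general

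*Protocol article*

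**What the plan says.** Section 2.7.2 (Analysis of efficacy endpoints) sets the rule for the two primary endpoints, change in NRS for radiating pain and in ODI from baseline to week 7: "Missing data will be handled via Mixed Model for Repeated Measures (MMRM), with sensitivity analyses using ANCOVA on datasets imputed by multiple imputations (MI". The same sentence then names LOCF as the second imputation for those sensitivity analyses. For the secondary endpoints the section repeats the arrangement: "Missing data will be managed via MMRM, with ANCOVA sensitivity analyses using MI and LOCF".

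Section 2.7.5 (Missing value management) gives one rule for both classes of outcome: "Missing data for primary and secondary outcomes will be managed using LOCF imputation, selected for its conservative approach in estimating treatment effects post-dropout". It states the assumption and the expected benefit: "assuming stable participant conditions after the last observation, ensuring robust and interpretable efficacy results". It mentions neither MMRM nor multiple imputation, and does not limit LOCF to a sensitivity role.

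Section 2.7 fixes the analysis set, "with ITT as the primary analysis and PP as supportive", but gives no order of precedence between the two missing-data rules. Neither does any other section.

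**The concern.** For the same endpoint, one section makes LOCF a sensitivity analysis and another makes it the main handling. The two rules cannot be run together as the main analysis: once LOCF has filled the gaps, the mixed model has no missing outcome left to deal with. They are two analyses that can give two week-7 differences, and the document lets either be called primary.

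Two things are at stake. First, a choice left open until the data are in can be made on the results. Second, if section 2.7.5 is followed as written, the primary estimate carries a bias that depends on how dropout differs between the arms, while the stated rationale tells the reader that it errs on the safe side.

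**Working it through.** **The two rules side by side**

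| | Section 2.7.2 | Section 2.7.5 |
|---|---|---|
| Primary endpoints | MMRM | LOCF |
| Secondary endpoints | MMRM | LOCF |
| Role of LOCF | ANCOVA sensitivity analysis, beside MI | the stated handling, with no limit |
| Role of MI | ANCOVA sensitivity analysis | not mentioned |

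The contradiction needs no arithmetic. The rest tests the claim that LOCF is conservative.

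**Inputs from the document**
- ODI and NRS are collected at weeks 0, 3, 5 and 7 (section 2.6), with week 5 by telephone (Table 1, note 6). LOCF to week 7 can therefore carry a value from week 0, 3 or 5.
- Attrition is 15% in the text of section 2.3 and 10% in Table 2. No split by arm is given.
- Yardstick: "We estimated the standard deviation (σ) to be 10 points and set the minimum detectable difference (δ) to be 5 points". The scale is not named, but an SD of 10 cannot arise on a 0–10 NRS, so ODI is the plausible reading.

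**Assumptions (the document gives no trajectory).** Mean ODI improvement is 5, 10 and 12 points at weeks 3, 5 and 7 in both arms. The true difference is 0.

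**Bias with unequal dropout rates.** If a share p of an arm drops out, last seen at week k with mean improvement m_k, the LOCF mean improvement is (1 − p) × 12 + p × m_k. With the same course in both arms, the spurious difference is (p_A − p_B) × (12 − m_k).

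| Last seen | 12 − m_k | 20% vs 10% | 25% vs 5% | 25% vs 5%, share of δ = 5 |
|---|---|---|---|---|
| Week 5 | 2 | 0.10 × 2 = 0.2 | 0.20 × 2 = 0.4 | 8% |
| Week 3 | 7 | 0.10 × 7 = 0.7 | 0.20 × 7 = 1.4 | 28% |
| Baseline | 12 | 0.10 × 12 = 1.2 | 0.20 × 12 = 2.4 | 48% |

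Both splits average 15%. The difference favours the arm that loses fewer people, and its sign reverses if the split reverses. With equal rates and equal timing it is 0.

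**Timing alone is enough.** With 15% dropout in each arm, one arm's dropouts last seen at baseline and the other's at week 5, the difference is 0.15 × 12 − 0.15 × 2 = 1.5 points.

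**Where LOCF does shrink the effect.** Assume a true benefit of 5, with improvement of 9 at week 3 and 17 at week 7 on herbal medicine, and 7 and 12 on control. Half of the dropouts are last seen at baseline and half at week 3.
- Dropout 15% in both arms: herbal 0.85 × 17 + 0.075 × 9 = 15.125; control 0.85 × 12 + 0.075 × 7 = 10.725; difference 4.4.
- Herbal 5%, control 25%: 16.375 − 9.875 = 6.5.
- Herbal 25%, control 5%: 13.875 − 11.575 = 2.3.

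Balanced dropout turns 5 into 4.4, which is conservative for superiority. Unbalanced dropout gives anything from 2.3 to 6.5. Swapping the arm labels in the balanced case, a true herbal deficit of 5 becomes 4.4, which moves away from the −10 ODI margin and so favours non-inferiority.

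**Type I error.** This was simulated with 37 per arm, 10,000 replicates, ODI means of 40, 33, 30 and 28 at weeks 0, 3, 5 and 7, SD 10, correlation 0.6, no true effect, and half of the dropouts last seen at week 0 and half at week 3.

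| Dropout, herbal vs control | LOCF-ANCOVA, two-sided 5% test |
|---|---|
| 10% vs 10% | 5.2% |
| 5% vs 15% | 7.4% |
| 5% vs 25% | 14.1% |
| 25% vs 5% | 13.9% |

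A baseline-adjusted analysis of the observed week-7 values stayed between 4.8% and 5.2%. In this simulation dropout depended only on arm, so that comparator is unbiased by construction. The comparison isolates what LOCF adds and does not show that MMRM is safe under every dropout mechanism.

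**The case against.** **Section 2.7.5 might only describe the sensitivity dataset.** This would remove the conflict, but the text does not bear it. The section is the general one on missing values, names primary and secondary outcomes, and presents LOCF as what makes the efficacy results robust. A separate analysis plan, not among the documents at hand, may settle precedence; that would not make these two sections agree.

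**LOCF can be conservative.** This stands in part. Superiority is the powered hypothesis, and with similar dropout in both arms LOCF pulls a true effect towards zero. A reader might infer that the rationale is simply false, or that LOCF must flatter herbal medicine. Neither follows: it fails as a general justification, and the bias can go either way.

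**Unequal dropout is assumed.** This stands. The trial is open-label, the burdens differ (30 days of oral medicine against up to 10 sessions), and the adherence rule for withdrawal in section 2.8 is worded differently for each arm. These make imbalance possible, but nothing in the document predicts a two- to five-fold difference. Section 2.8 also allows follow-up with consent after treatment ends, so stopping treatment need not mean a missing week-7 value.

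**The largest figures are extreme.** This stands. The 2.4 points require every dropout to have no value after baseline. The week-5 telephone assessment needs no clinic visit and may often supply a closer value, which brings the same split down to 0.4.

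**Single imputation understates the standard error.** True in principle, but not shown to matter here: with equal dropout the simulated error rate was 5.2%. The inflation seen with unequal dropout reflects bias.

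**Non-inferiority adds little weight.** This stands. Section 2.3 declares that analysis exploratory and underpowered.

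**Conclusion.** The contradiction holds on the text alone. Two sections give different main handling of missing data for the same primary and secondary outcomes, with no rule of precedence, so the primary estimate is not uniquely fixed. Because this concerns the primary analysis and recruitment is under way (section 2.2), it should be settled before outcome data are examined.

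The rationale for LOCF does not hold in general. If patients improve over seven weeks, LOCF is conservative for superiority under balanced dropout, and biased for or against herbal medicine when the rate or timing of dropout differs. Under the assumed course with no true difference, the spurious ODI difference is 0.2 to 1.2 points at 20% against 10% and 0.4 to 2.4 points at 25% against 5%. It is 0 with equal dropout of equal timing. These sizes illustrate the mechanism and are not forecasts, because the document gives neither an ODI course nor a dropout split. The bias argument alone would be a lesser point; the unsettled primary method is what makes the change necessary.

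**What to change.** Rewrite section 2.7.5 so that it agrees with section 2.7.2:
- State MMRM on observed data as the single primary handling of missing outcomes, using the post-baseline visits at which each outcome is collected, with the week-7 contrast as the primary estimate for NRS radiating pain and ODI.
- Delete the statement that LOCF is conservative and the claim of robustness that rests on it.
- Confine LOCF to the sensitivity role it already has in section 2.7.2, or drop it in favour of the multiple imputation already listed there.

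A delta-adjusted multiple imputation would be a useful optional addition, since MMRM relies on data being missing at random. It is not needed to resolve the contradiction, and the exact model terms can be left to the analysis plan.

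The cost is one paragraph. No new data, visits or participants are needed.
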